### Audit of the quality of the data included in the primary endpoints’ calculation

The patient data measured by the CFCs (height, weight, and FEV1 [per L]) for 2012 and 2013 underwent an on-site quality audit at the 14 CFCs in the PHARE-M Group. It was the first on-site audit ever performed to establish the quality of these indicators. The objective was not to comprehensively audit all data for the patients included in the study. Rather, the objective was to comprehensively identify the different causes of error due to failures in the processes of measuring and/or selecting the values transmitted to the Registry in order to identify avenues for improvement of the quality of the data in the Registry. The sample of patients whose data were audited thus had to reflect the distribution by age range of the patients at each CFC (20 records/CFC) in order to cover the different measurement procedures defined by international benchmarks [13–15] and the data selection rules defined by the French Patient Registry Steering Committee, and to offer every opportunity to reach saturation of the various causes of error [16]. They will be taken into account in the interpretation of the results of the quantitative study.

## Qualitative study

### Design

The design refers to the modeling of the intervention [11] including the contextual elements and the mechanisms shown in Fig. 3.

**Fig. 3 Fig3:**
[figure not shown]
Modeling of the intervention, context, and mechanisms

The PHARE-M intervention consisted of establishing, training and coaching a quality team (QT) at each CFC comprising a number of professionals from the multidisciplinary CF team and 1 parent or patient from the CFC’s caseload. The members of the QT have been trained in quality methods and tools and coached in changing care processes. The PHARE-M intervention should have directly impacted the ability of the local QT to master QI methods and tools, lead changes in the care processes, and should have generated good appreciation of the utility of the QT efforts. This direct impact of PHARE-M is identified under the heading “QT effectiveness”. QT effectiveness may not only be the result of the PHARE-M intervention but may have been modulated by internal mechanisms, such as the composition of the QT (number of members and disciplines enlisted), its functioning (rigor in the QI work, decision-making, clarity of the roles…) and the parent or patient engagement. Those mechanisms are represented as impacting QT effectiveness (Table 3). Beyond the ability to master the QI methods and tools, the PHARE-M intervention was expected to have an impact on the quality of CF care delivered at the CFC. The Chronic Care Model [12] was deemed appropriate to account for quality of CF care across the 6 dimensions: existing improvement goals, multidisciplinary care, self-management support, decision support (use of evidence-based guidelines), use of information system and electronic patient record, and organization of resources in the patient’s community of life. Finally, an indirect impact of the PHARE-M intervention is expected on the trend in patient outcomes’ evolution as measured in the quantitative part of this study. Moreover, some elements in the CFC contexts, which are external to the PHARE-M intervention and preexisted to its introduction, may have had a major impact both on the adherence of the team to the QI work and on its outputs. The contextual elements that have been brought in this study include the composition of the MDT, the leadership, the patient-centeredness of care, the innovative culture of the team, and the support from the hospital quality department.

The qualitative study will test these hypotheses using a questionnaire to be self-administered, in 2015, to all members of the MDT at the 14 CFCs and to the patients/parents participating in the quality teams.

Quality of care has been defined according to the criteria of the Chronic Care Model [12]; as this model has not been popularized in France nor in cystic fibrosis, we adapted it with 47 items aimed at characterizing CF care. Table 4 presents a list of these items.

**Table 4 Tab4:** Criteria for quality of CF care derived from the chronic care model

IG — Improvement Goals at the CFC	1 — There are improvement goals at the CFC
	2 — These goals, if they exist, are the subject of both indicators and an action plan at the CFC
	3 — The CFC has tools to follow up this action plan in the form of a dashboard
	4 — To your knowledge, this action plan has been discussed with management and validated
SMS — Self-Management Support - Therapeutic Patient Education	1 — To your knowledge, there is a therapeutic education program for patients at the CFC authorized by the French regional health agency (ARS)
	2 — In your opinion, the professionals at the CFC are well trained in TPE
	3 — More than 80% of the patients/parents attended at least one TPE session in the last year
	4 — The total time spent by the professionals on TPE is sufficient
	5 — There are no obstacles to implementing TPE at the CFC
	6 — The team is involved in the studies of one of the French national groups on therapeutic education via face-to-face participation or regular reporting of information
	7 — The CFC has priority objectives for developing TPE
	8 — If yes, the CFC has indicators to follow up the achievement of these priority objectives
MM — Multidisciplinary management	1 — To your knowledge, the multidisciplinary team at the CFC comprises all the disciplines recommended by the French National Diagnosis and Treatment Protocol (PNDS): specialist physician, nurse, physiotherapist, psychologist, secretary, and social worker
	2 — The number of staff in all disciplines is sufficient for the number of patients followed up
	3 — In your view, the multidisciplinary team seems stable over time (the professionals’ turnover rate is below 20% in a year)
	4 — The members of the multidisciplinary team have a great deal of expertise in managing cystic fibrosis
	5 — The multidisciplinary team meets often enough to perform a summary of the records of the patients who have come to the CFC
	6 — During these multidisciplinary meetings, the team generally reviews the records of the patients with a scheduled visit to the CFC
	7 — During these multidisciplinary meetings, the team regularly examines the patients’ educational needs and the outcomes of the educational sessions held
	8 — The scheduled consultation is genuinely multidisciplinary: the patient meets with at least the physician, the nurse, and the physiotherapist
	9 — The scheduled consultation allows the patient to meet with a professional other than the ones mentioned above, as required (dietician, psychologist, or social worker)
	10 — The scheduled consultation allows the patient to benefit at least once per year from a TPE session on a priority objective for him or her
	11 — When a patient requires it, the CFC is able to call upon a network of referent professionals in other disciplines with knowledge of cystic fibrosis (geneticist, endocrinologist, ENT, gastroenterologist, etc.)
	12 — It is possible to be managed at the CFC on a 24/7 basis
	13 — Patients who arrive at the hospital emergency department are managed in accordance with a protocol established by the CFC with the emergency department for patients suffering from cystic fibrosis
	14 — The team regularly holds a meeting to discuss its functioning and the problems at the CFC in order to improve care management
DS — Therapeutic decision support (guidelines)	1 — The team manages the availability of guidelines (nutritional, respiratory, hygienic, etc.) in a way that they are accessible to all professionals
	2 — The team has defined an internal reporting procedure to insure that care management recommendations (guidelines) updates are accessible to the team
	3 — The team systematically verifies for each patient that the latest recommendations are applied and/or offered to him or her
	4 — The team uses alerts on the population followed up to verify that the latest recommendations for care are applied to the eligible patients (e.g. glucose tolerance test alert, vaccination alert, examination alert, etc.)
	5 — The team has optimally organized the multidisciplinary consultation process (circuit, schedules, chain of professionals, cross-contamination, hazards, etc.) to deliver high quality of care.
	6 — The team has optimally organized the process of responding to telephone or email messages from the patients and families
IS — Patient information system	1 — The team uses an electronic cystic fibrosis patient record
	2 — The team has an electronic patient record system that allows it to view changes in the patient health outcomes (nutritional and respiratory outcomes) over the course of several years
	3 — The team uses the electronic patient record system during the multidisciplinary staff meetings
	4 — The team displays information from the electronic patient record during the multidisciplinary meeting (graphs of changes over time, reports from previous consultations with different professionals, etc.)
	5 — The team uses the electronic patient record system both to create alerts on applying recommendations for the patient and to compile statistics on the population followed up
	6 — The team uses the electronic patient record system to include biology results
	7 — The team uses the electronic patient record system to include imaging results
	8 — The electronic patient record system helps in selecting patients for clinical trials
	9 — The electronic patient record data are automatically transmitted with a good degree of reliability (minimal verifications, corrections, and additions) to the French Cystic Fibrosis Registry
SN — Staff in the networks in the community	1 — The CFC has organized a network of professionals in the patient community for managing care at home
	2 — The CFC organizes regular trainings for professionals in the patient community
	3 — The CFC regularly evaluates the professionals caring for CF patients in the community
	4 — The CFC assesses the health providers of devices managing CF patients
	5 — The CFC assesses the needs for home care and its distribution between professionals and carers for a balanced organization of home care
	6 — The CFC provides the patients with offers of sports activities, creative activities, and psychological support near their place of residence

QT effectiveness has been described in the studies by Lemieux-Charles [17] and Shortell [18]: it is characterized according to 27 items (see Table 5).

**Table 5 Tab5:** Effectiveness of a quality team (QT)

Command of the quality process and tools	1. The teams that implement a quality process have a clear vision of the area on which to focus their improvement efforts and the expectations to be met. When you started the project, did you have such a vision?
	2. The quality teams sometimes use a method for making progress, such as a guide to follow step by step which helps them organize their work. Did your team use such a structured method?
	3. Did your team make one or more changes in its way of working?
	4. Did the team analyze data to ensure that such change(s) indeed represented an improvement?
	5. Did the team try to understand variations in the CFC processes and the reasons that could account for them (variations over time or between professionals, time of year, patient characteristics, etc.)?
	6. Does the team routinely have data allowing it to make a state of play and identify problems?
	7. Did the team have to develop a system to collect specific data (such as questionnaires, audits, interviews, or measurements) to identify problems and assess the responses provided?
	8. Did the team establish a data collection system to continue to manage quality or monitor the new processes established?
	9. Was the team able to rely on a referent professional to coordinate the meetings and work of the quality team?
	10. Was the team able to rely on a referent professional to collect and analyze data?
	1. The team was able to perform measurements to define and assess changes within the framework of tests.
Capacity to drive change	2. After testing a change, the team succeeded in discussing the outcomes observed and learning from this test.
	3. The team succeeded in analyzing the outcomes of the test to propose new changes or adjustments to be tested.
	4. During the process, the team was able to easily incorporate and adapt ideas for changes to meet the organization’s needs.
	5. The team was able to enlist sufficient knowledge and skills to drive change under good conditions.
	6. The team could find sufficient assistance in the hospital to support changes.
	7. The team could sufficiently rely on the support of the French national team to make changes at the CFC.
Effectiveness perceived by the quality team	1. The performance of the PHARE-M steering team met my expectations.
	2. I was satisfied with my experience as a member of the quality team.
	3. I believe that my participation was useful and positive for the work of the team.
	4. I would be willing to participate again on a similar team to work on quality improvement.
	5. I believe that the work of the quality team was useful for improving quality.
	6. The outcomes achieved through the work of the quality team meet the organization’s needs for improvement.
	7. It is necessary to maintain an ongoing quality improvement process to continuously improve care at the CFC.
Effectiveness perceived by the rest of the team	1. I believe that the work of the steering team was useful for improving quality at the CFC.
	2. I believe that the entire team at the CFC was enlisted and contributed to quality improvement.
	3. I believe that the outcomes achieved collectively meet the organization’s needs for improvement.
	4. I believe that it is necessary to maintain an ongoing quality improvement process to continuously improve management at the CFC.

QT Internal factors that may have modulated the QT effectiveness: QT functioning [17] is characterized by 22 items classified in 4 categories 1) the organization at work, 2) the decision-making process, 3) the shared improvement goals, and 4) the ability to communicate and get external support. Studies by L. Lemieux-Charles defined these items to analyze the impact of adopting quality improvement practices on the internal functioning of a team. We use the same items to analyze if the team’s functioning could modulate its effectiveness (see Table 6).

**Table 6 Tab6:** Internal functioning of the quality team (QT)

Strictness of organization and clarity of roles	1. The leader was clear and explicit on how he or she wanted the team to work.
	2. The leader reviewed the steering team’s work and asked how we were going to go about it.
	3. The leader also requested the opinion of the other members of the team.
	4. The leader’s behavior reflected the importance he or she placed on the quality team functioning well.
	5. Our team could have been better at seeking help and securing more skills to do the work.
	6. Sometimes it seemed that we were working or going about the matter in the wrong way.
	7. Roles were so unclear that the work of different individuals seemed to overlap.
	8. The members of the team had different outlooks and experiences and came from different disciplines.
Decision- making on the QT	1. Most of the members of the team had an opportunity to participate in decision-making.
	2. We appreciated our differences, which shaped our decisions.
	3. The contribution of each member of the team was heard and taken into consideration.
	4. We examined many different ideas before making a decision.
	5. Our team possessed sufficient resources and skills and applied them well enough to work properly.
	6. Our team worked well enough to accomplish its mission satisfactorily.
Clarity of objectives	1. The members of the team were in agreement on the objectives of the project.
	2. The achievement of the objectives guided the activities of the members of the team.
	3. The members of the team did what was expected of them.
	4. The members of the team were all focused on the achievement of the same objectives.
Communication and cooperation	1. There was a great deal of cooperation between the different hospital departments.
	2. In this hospital, most departments and services have a hard time sitting down at a table and solving problems together.
	3. The people I worked with were comfortable with suggesting changes and improvements.
	4. Our team received all the information required to plan and organize its work.

The engagement of the patient/parent as characterized in Carman’s framework [19] is assessed by a list of 31 items, prepared as part of this research (see Table 7).

**Table 7 Tab7:** Engagement of the patients/parents on the quality team (QT)

Information and activation of the patients/parents	1. The patients and parents are educated regularly (annually or more often) by the team about general subjects concerning cystic fibrosis care and research.
	2. The patients and parents are rather familiar with general cystic fibrosis information: research, progress made, and Registry data.
	3. The CFC team has educated the patients and parents about the PHARE-M’s importance and aim.
	4. A good relationship between the patient or parent recruited and the team is indispensable for the patient or parent to participate in the PHARE-M.
	5. The patient or parent recruited is well informed of the challenges (10 commitments) of management quality.
	6. The presence of a patient or parent on the steering team is a given and an asset.
	7. The place of a parent or patient is not on a quality team, because he or she does not have enough training or education.
	8. The place of a parent or patient is not on a quality team, because he or she already has too many personal problems to manage.
	9. The patient or parent recruited possesses the qualities to become a member of the steering team.
	10. The patient or parent recruited must have developed coping skills (see therapeutic education standard: knowing how to manage emotions and stress; solving problems, making decisions, and making choices; knowing how to communicate and being adept in relationships with others; and knowing how to put oneself in the place of others).

The context elements include: the composition of the multidisciplinary team at the beginning of the PHARE-M intervention (2011) because it might have been a limiting factor in assigning staff to the QT; the culture of the microsystem to which the QT belongs [18] i.e. the organizational culture (see Table 8) and patient centeredness and leadership style (see Table 9); the alignment of the PHARE-M QIP with the hospital quality policy as described within the framework of the European QUASER study [20] using eight open questions in an interview with a head of the hospital quality department (see Table 10).

**Table 8 Tab8:** Organizational culture

*Organizational culture:*	
Research studies have defined four types of organizational culture, arising from both the organization’s external environment and internal management: a “familial” type, an “entrepreneurial” type, a “prescriptive” type, and a “productive” type. The five rubrics below describe the characteristics associated with these different types of organization. You have 100 points to distribute among the four proposals based on the degree to which they resemble your organization. For example: If the CFC resembles Description A a great deal and Description B a little, and does not resemble Description C or Description D at all, assign 70 points to Response A and the 30 remaining points to Response B.	
§1. Character	1. Organization A is very familial, like a big family. People seem to share a lot of themselves.
	2. Organization B is very dynamic and entrepreneurial. People seem to want to venture off the beaten path and take risks.
	3. Organization C is very structured and formalized. Procedures govern people’s work.
	4. Organization D is very focused on production, with the concern being that the work gets done. Individuals are not very personally involved.
§2. Management	5. Organization A’s director(s) are warm and attentive. They try to develop people’s potential and act as mentors or guides.
	6. Organization B’s director(s) take risks. They encourage people to be innovative and to try out new ideas by taking risks.
	7. Organization C’s director(s) enforce rules. They expect people to strictly apply policies and procedures.
	8. Organization D’s director(s) resemble coordinating coaches. They help people achieve the organization’s objectives.
§3. Cohesion	9. Organization A’s factors for cohesion are loyalty and tradition. Dedication to the organization is high.
	10. Organization B’s factors for cohesion are the race for innovation and development. There is a desire to be the first.
	11. Organization C’s factors for cohesion are hierarchical rules and establishment policies. Maintaining suitable functioning is important here.
	12. Organization D’s factors for cohesion are the achievement of objectives and the performance of required tasks. This vision of production is shared.
§4. Emphasis placed on...	13. Organization A emphasizes human resources. Having strong cohesion and a high sense of morale are important.
	14. Organization B emphasizes growth and acquisition of new resources. Being ready to rise to new challenges is important.
	15. Organization C emphasizes permanence and stability. Complying with rules and performing operations smoothly are important.
	16. Organization D emphasizes competition to achieve objectives. Measuring results is important.
§5. Recognition of efforts	17. Organization A recognizes all its members’ efforts equally. It is important that everybody in the pyramid, from the very top to the very bottom, is treated as equally as possible.
	18. Organization B rewards individual initiative. Those who have the most ideas and perform the most innovative actions receive the most recognition.
	19. Organization C modulates recognition based on rank. The higher your position, the more your efforts are recognized.
	20. Organization D rewards the achievement of objectives. Individuals who demonstrate leadership and thus help achieve objectives are recognized.

**Table 9 Tab9:** Patient-oriented culture and leadership

Patient-oriented organization	1. Our organization works to properly identify patient needs and expectations.
	2. The professionals handle patient requests promptly.
	3. Patient complaints are analyzed to identify recurring causes and prevent problems from being replicated.
	4. The organization uses data from the patients themselves to improve services.
	5. The organization uses data regarding patient satisfaction and/or patient expectations to improve services.
Leadership at the CFC	1. The leader develops interesting/exciting opportunities for our organization.
	2. The leader proposes new and even innovative ideas to improve management services and processes.
	3. The leader drives the organization to meet patient needs and ensures management/care safety.
	4. The leader takes into account the needs of both the service and the staff during major changes within the organization.
	5. The leader builds close, positive relationships with the other departments in the hospital.
	6. The leader builds close cooperative relationships with other organizations outside the hospital.

**Table 10 Tab10:** Open-ended questions to the hospital’s quality department

1. What are the priorities of the hospital’s quality department?	
2. Support for care services in quality improvement: was another quality program developed for another disease or another care service?	
3. How are patients included in the different committees and groups working to improve quality in the hospital?	
4. How is quality measured (main indicators)?	
5. What training programs in quality tools and methods are promoted by the hospital?	
6. How was the quality department informed of the PHARE-M (by whom and when)?	
7. What were the reasons for the quality department’s engagement (or non-engagement) in the PHARE-M, in support of the CFC? In the case of engagement, what resources and time were dedicated to supporting the CFC?	
8. How is the PHARE-M perceived by the quality department management in terms of coherence with hospital policy, perceived effectiveness, and other matters? If necessary, the example of another quality improvement program rolled out in the hospital can be cited.	

Focus groups with the members of each QT were conducted by the Clinical Research Assistant, designed around four open-ended questions: 1) What changes in the organization of the CFC can be attributed to the PHARE-M? 2) What difficulties were faced at the CFC? 3) What successes were achieved? and 4) What lessons from this experience after 3 to 4 years? The results of these focus groups involving the 14 CFCs will be put in perspective with the results of the survey conducted by one assessor of the pilot phase who interviewed the 7 first CFCs on the following themes: 1) PHARE-M applicability, 2) participation of patients and parents, 3) functioning and coordination, 4) perceived benefits and costs, 5) effect on the team, 6) effect on care management, and 7) recommendations for PHARE-M national deployment.

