In 2011, the French national team at the Nantes/Roscoff CF-CERD transposed the PHARE-M quality improvement program from the US CFF QIP model (*PHARE-M: Programme Hospitalier d’Amélioration des Résultats et de l’Expertise en Mucoviscidose - Hospital Program to Improve Outcomes and Expertise in Cystic Fibrosis)*. It was launched in September 2011 with a pilot phase (2011–2012) involving seven volunteer CFCs, which underwent two external assessments, leading to certain adjustments to the initial program. This adjusted version was deployed during a regional expansion phase (2012–2013), including seven more CFCs before its national deployment [10]. The main adjustments consisted in more practical exercises during face-to-face meetings (less theoretical presentations), more on-site coaching to help the quality teams analyze their processes of care, and the designation of a PHARE-M referent in each local team to keep focused on the QI work. These 2 years are called the “experimental phase”, which involved 14 CFCs.

The two evaluations at the end of the one-year pilot phase showed the progressive adherence of the teams and improvements in care management, but a limited impact on patient health outcomes. They also highlighted that the adherence to the program mainly depended on the motivation of the multidisciplinary team (MDT), especially its lead physician. The lack of resources at some CFCs was raised to account for variations in the teams’ engagement as the level of available staff seemed to influence the extent to which the team was effectively enlisted. The participation of a patient or parent in each local quality team varied depending on the cultural context of the centers, some being used to share information with patients/parents, having a patient group in the CF center for years, others being involved in patient therapeutic education while others were acting in a more partenalistic model of care. The support received from the hospital quality department in two hospitals was emphasized as a factor that facilitated the adoption of quality tools by the teams. The recommendation of the assessor was to evaluate the impact of the program on patient outcomes by 2015.

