### Expected results in terms of quality improvement of care

If the research study enables to identify factors promoting the adoption of the PHARE-M QIP and the maximization of its impact at CFCs, attention must be paid to the contextual elements to be worked on before or in parallel with the introduction of this program at the remaining CFCs. In the United States, the CFF has conducted “Leadership Collaborative” programs to develop leadership on multidisciplinary teams. The availability of the MDTs staff at the European standards for the number of patients followed could also represent a pre-requisite for their participation in the PHARE-M. The quality of care assessed after 3 years within the CFCs trained to PHARE-M might also enable to identify new avenues for improvement, including some beyond the scope of the clinical microsystem such as the Information System or the generalization of Guidelines.

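### Leadership, patient-centeredness and innovative culture are called pre-existing context but are measured only in 2015, so the direction of any association with them cannot be inferred

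*Protocol article*

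**What the plan says.** The Design section of the qualitative study sets out a model of intervention, mechanisms and context. It names the context as follows: "The contextual elements that have been brought in this study include the composition of the MDT, the leadership, the patient-centeredness of care", together with the team's innovative culture and support from the hospital quality department. It describes these as elements "which are external to the PHARE-M intervention and preexisted to its introduction, may have had a major impact" on adherence to the QI work and on what that work produces. The same section says the hypotheses will be tested "using a questionnaire to be self-administered, in 2015, to all members of the MDT at the 14 CFCs" and to the patients or parents on the quality teams.

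The paragraph introducing Tables 8 to 10 dates one element only: "the composition of the multidisciplinary team at the beginning of the PHARE-M intervention (2011", on the ground that it could have limited the staff available for the quality team. Organizational culture is referred to Table 8, and patient-centeredness and leadership to Table 9, with no date.

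The section on analyses of responses plans a descriptive search for associations of quality of care with quality team effectiveness, patient or parent engagement and context. It then plans a signature set of factors linked to maximum or minimum impact. The section on expected results says that, if such factors are found, "attention must be paid to the contextual elements to be worked on before or in parallel with the introduction of this program" at the remaining centers.

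**The concern.** A factor can be read as a pre-existing determinant only if it is known to have stood before the exposure. These three are recorded once, after exposure, at centers that had all been through the program. If working with PHARE-M raised some of the scores, an association with impact would reflect the program's own effect. If the scores were already high in 2011, the same association would reflect context. One 2015 reading cannot separate the two.

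The stake is practical. The study is meant to tell the remaining centers what context to attend to, and the expected-results section moves straight from context to US programs that develop leadership. A reader of the results would naturally take a leadership or patient-orientation score in the signature as something to have in place at the start.

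**Working it through.** No sample size or error rate is involved. The check compares dates and item wording.

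**1. How each context element is dated**
- Team composition: start of the intervention, 2011.
- Leadership and patient-centeredness: Table 9, 2015 questionnaire.
- Innovative culture: Table 8, 2015 questionnaire.
- Hospital quality department support: separate open-question interview (Table 10), with some questions about the past.

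So three of the five elements have no date before the program. They yield six scores: four culture types, patient orientation and leadership.

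**2. Time from program start to measurement**
- First seven centers ("It was launched in September 2011 with a pilot phase (2011–2012) involving seven volunteer CFCs"): September 2011 to January 2015 is 3 + 4/12 = 3.3 years; to December 2015 it is 4 + 3/12 = 4.25, about 4.3 years.
- Next seven ("This adjusted version was deployed during a regional expansion phase (2012–2013), including seven more CFCs"): the month is not given. Assuming September 2012, the interval is about 2.3 to 3.3 years. For a start within 2013, it runs from December 2013 to January 2015 (1 + 1/12 = 1.1 years) up to January 2013 to December 2015 (2 + 11/12 = 2.9 years).

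Roughly 2 to 4 years is a fair summary. The article itself speaks of 3 years, and of 3 to 4 years in the focus-group questions.

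**3. Could an earlier score exist?** The section on instrument development says the questionnaire was prepared from January to June 2014 and tested from July to September 2014 in three teams. The latest start compatible with a 2012–2013 expansion is December 2013. No center can therefore have a pre-program score on this instrument, whatever start month is assumed.

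**4. Recall frame.** Many quality team items in Tables 5 and 6 are in the past tense and look back over the project. The items in Tables 8 and 9 are in the present tense and do not refer to 2011. As printed, they ask what the center is like in 2015.

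**5. Overlap with the intervention.** PHARE-M trained teams in quality methods, coached changes in care processes and placed a patient or parent on each quality team. Table 9 has five patient-orientation items and six leadership items. Three of the five (analysing complaints for recurring causes, using data from patients, using satisfaction or expectation data) and one of the six (a leader proposing ideas to improve services and processes) describe similar activity. That is 3 + 1 = 4 of 11 items. Others, such as relations with organizations outside the hospital, do not obviously overlap. Quality team members receive the whole questionnaire, so their context scores and effectiveness scores come from the same people at the same time.

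**6. Culture types.** Each of the five rubrics in Table 8 divides 100 points among four descriptions. If one type gains *d* points, the other three together lose *d*. The four scores cannot all rise, and nothing in the article says which type PHARE-M would favor.

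**7. Acknowledgement.** The sections on scope and on limitations discuss volunteer centers, residual baseline differences, data quality and the number of respondents. Neither mentions that these context measures postdate the program.

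**The case against.** The planned analysis is associational. It is called descriptive, it searches for potential associations, and no causal or mediation model of context is specified. The Design section says only that context may have had an impact. The roll-out sentence is conditional and allows work on context alongside the program as well as before it. The term pre-requisite is applied only to staffing, and team composition is the element dated to 2011. The full questionnaire and Fig. 3 are not shown, so a recall instruction cannot be ruled out.

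Most of this stands and limits the point. It does not remove it, because the Design section fixes a time order, external and earlier, that the measurement cannot support. A recall instruction, if there is one, would give recollections collected years later, not a baseline.

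A reader might go further and infer that PHARE-M raised these scores, so that the study will recommend as prerequisites what the program itself produced. The documents do not support that. No section reports a change in culture, leadership or patient orientation. The direct effects the model expects concern mastery of QI methods, leading change in care processes and perceived usefulness; beyond these it expects effects on quality of care and patient outcomes. For the four culture scores not even a direction can be given.

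**Conclusion.** The point holds as a matter of timing and labelling. Three of the five context elements, giving six scores, are described as preceding PHARE-M but are observed only in 2015, roughly 2 to 4 years after it began. The upper end rests on the stated September 2011 launch; the lower end assumes a September 2012 start for the second seven centers. For Table 9, where some items overlap with program content, an association may run either way. For Table 8 the order is equally unknown and no bias direction can be claimed. No size of bias can be calculated, since there is no earlier measurement to compare with.

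This affects the interpretation of the qualitative associations, the signature and the roll-out advice. It does not touch the cohort, the FEV1 and BMI endpoints or the comparison of slopes.

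**What to change.** - In the Design section and the paragraph introducing Tables 8 to 10, describe the Table 8 and 9 scores as post-intervention states recorded in 2015. Reserve the term pre-existing for elements dated or documented as prior: team composition in 2011, and center type and size. State the year used for size, because the pairing section works from 2012 Registry data.
- Keep the 2015 scores in the association analysis, but report them as concurrent correlates whose direction cannot be inferred. In any signature, show them separately from the pre-dated factors.
- In the expected-results section, do not present them as conditions that must be met before the program starts. They may still be reported as features found alongside greater or lesser impact.
- Pilot-phase assessment material may serve as early evidence for the first seven centers, labelled as collected at the end of the pilot year and not as baseline.
- Add a sentence on this timing to the limitations.

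The cost is some rewording and a regrouped presentation of results, with no new data collection. The price is a narrower conclusion about context: the study could say which 2015 traits go with greater impact, but not which came first.
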